**10.6. Study cohorts to be evaluated****10.6.1. Total Vaccinated Cohort**

The Total Vaccinated Cohort will include all vaccinated subjects for whom data are available. Thus, the total analysis of safety will include all subjects with at least one vaccine administration documented and the total analysis of immunogenicity will include vaccinated subjects for whom data concerning immunogenicity endpoint measures are available. The Total Vaccinated Cohort analysis will be performed per treatment actually administered.

**10.6.2. According to protocol (ATP) cohort for analysis of safety**

The ATP cohort for analysis of safety will include all evaluable subjects;

- who have received at least one dose of study vaccine according to their random assignment
- have sufficient data to perform an analysis of safety (at least one vaccine dose with safety follow-up)
- for whom administration site of study vaccine is per protocol
- who have not received a vaccine not specified or forbidden in the protocol and for whom elimination criteria were not applied
- for whom the randomization code has not been broken except for when unblinding has been carried out by the DSMB for Safety Analysis.
- who meet all eligibility criteria.

**10.6.3. According to protocol (ATP) cohort for analysis of immunogenicity**

The ATP cohort for analysis of immunogenicity will include all evaluable subjects (i.e. those meeting all eligibility criteria, complying with the procedures defined in the protocol, with no elimination criteria during the study) for whom data concerning immunogenicity endpoint measures are available.

**10.7. Derived and transformed data**

- Seroprotection rate for anti-HBsAg is defined as the percentage of subjects with antibody titers greater than or equal to an established cut-off (anti-HBsAg  $\geq 10$  mIU/mL).
- A subject seropositive for anti-CS antibody is a subject whose antibody titer is greater than or equal to the cut-off value (anti-CS  $\geq 0.5$  EU/mL).
- The Geometric Mean Titers (GMTs) calculations are performed by taking the anti-log of the mean of the log10 titer transformations. Antibody titers below the cut-off of the assay will be given an arbitrary value of half the cut-off for the purpose of GMT calculation.

For a given subject and a given immunogenicity measurement, missing or non-evaluable measurements will not be replaced. Therefore, an analysis will exclude subjects with missing or non-evaluable measurements.

**10.8. Final analyses**

The final analysis will be conducted on data collected until Day 90 (30 days post Dose 3). The study will continue in a single blind manner for additional safety surveillance and immunogenicity assessment. This additional information will be appended to the study report.

### **10.8.1. Analyses of safety**

#### **10.8.1.1. Primary endpoint**

For the safety primary endpoint, the occurrence of SAEs will be evaluated on the Total Vaccinated Cohort. The proportion of subjects with an SAE, classified by the MedDRA preferred term level, reported from study start until study conclusion (end of the double-blind phase) will be tabulated with exact 95% CI. Comparisons between groups will be done using Fisher's Exact test for each preferred term.

For the primary immunogenicity endpoint, for anti-CS GMTs 1 month post Dose 3, the assessment of non-inferiority of the RTS,S/AS01E group versus the RTS,S/AS02D group will be performed by comparing the upper limit of the 95% CI on the ratio of GMTs (RTS,S/AS02D / RTS,S/AS01E group) with a pre-defined non-inferiority limit, set at 3. The analysis will be performed on the ATP cohort for immunogenicity. If more than 5% of subjects are excluded from the ATP cohort for immunogenicity, a second analysis will be performed on the total vaccinated cohort.

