### 2.3. Tertiary objectives

- To assess, for RTS,S/AS01E when administered as 3 doses intramuscularly on a 0, 1, 2-month schedule to children aged 18 months to 4 years living in a malaria-endemic area:
  - safety between 1 month post Dose 3 until 12 months post Dose 3.
  - humoral immune response to CS antigen at 12 months post Dose 3
  - humoral immune response to HBs antigen at 12 months post Dose 3.

Refer to Section 10.3 for definitions of tertiary endpoints.

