## **10. DATA EVALUATION: CRITERIA FOR EVALUATION OF OBJECTIVES**

### **10.1. Coprimary endpoints**

#### **10.1.1. Safety**

- Occurrence of SAEs from the time of first vaccination (Study Month 0) until one month post Dose 3 (Study Month 3).

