#### **10.3.2. Safety**

- Occurrence of SAEs from 1 month post Dose 3 until 12 months post Dose 3.

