**10.5.1. Sample size for the primary safety endpoint**

Safety analyses will be performed on the Total Cohort. A trial of this size has the power to detect only large differences in the frequencies of AEs with reasonable power. A sample size of 75 evaluable subjects per group has the power to detect differences in the rates of safety endpoints between groups as shown in Table 11. Comparisons between groups will be done using Fisher's Exact test for each AE coded by preferred term (alpha = 0.05, 2 sided).

**Table 11 Differences in safety endpoints (between treatment groups that can be detected with 90% power for varying baseline rates)**

| Frequency of events for RTS,S/AS02D | Frequency of events for RTS,S/AS01E | Power to detect difference (number per group equals 75) |
|-------------------------------------|-------------------------------------|---------------------------------------------------------|
| 1%                                  | 13%                                 | 90%                                                     |
| 3%                                  | 18%                                 | 90%                                                     |
| 5%                                  | 21%                                 | 90%                                                     |
| 10%                                 | 29%                                 | 90%                                                     |

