## **10.9. Annex analysis at study conclusion**

### **10.9.1. Analyses of safety**

The analysis of the occurrence of SAEs will be performed on the Total Vaccinated Cohort. The proportion of subjects with an SAE, classified by the MedDRA preferred term level, reported from study start until study conclusion (end of the single-blind phase) will be tabulated with exact 95% CI. Comparisons between groups will be done using Fisher's Exact test for each preferred term.

Serious adverse events and withdrawal due to adverse event(s) will be described in detail.

Biochemistry (ALT, creatinine) and hematology (hemoglobin, WBC, platelets) values that are outside of the reference ranges will be described for Clinic Visit 9 (end of single-blind phase).

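### The SAE analyses do not match the SAE endpoints: Months 3 to 14 are never estimated on their own, and the any-SAE coprimary endpoint is compared only term by term

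*Protocol*

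**What the plan says.** **Endpoints.** Protocol 10.1.1 defines the coprimary safety endpoint as "Occurrence of SAEs from the time of first vaccination (Study Month 0) until one month post Dose 3 (Study Month 3"). It is not divided by type of event. Protocol 10.3.2 defines the tertiary safety endpoint as "Occurrence of SAEs from 1 month post Dose 3 until 12 months post Dose 3", and the tertiary objective in 2.3 gives the same period: "safety between 1 month post Dose 3 until 12 months post Dose 3".

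**Analyses.** For the coprimary endpoint, 10.8.1.1 tabulates, with an exact 95% CI, "The proportion of subjects with an SAE, classified by the MedDRA preferred term level, reported from study start until study conclusion (end of the double-blind" part of the study). The only between-group comparison is "Comparisons between groups will be done using Fisher's Exact test for each preferred term". Section 10.5.1 plans the same for adverse events: "Comparisons between groups will be done using Fisher's Exact test for each AE coded by preferred term (alpha = 0.05, 2 sided"). At study end, 10.9.1 says the proportion with an SAE, by preferred term, "reported from study start until study conclusion (end of the single-blind phase) will be tabulated with exact 95% CI", again with one Fisher test per term.

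No SAE analysis in the protocol starts at Month 3, and none compares the groups on children with at least one SAE. Section 10.8.1.2, by contrast, does define at-least-one and any-event summaries for the secondary safety endpoints.

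**The concern.** In two places the analysis answers a different question from the one the endpoint asks.

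For the tertiary endpoint, safety after the vaccination phase is a separate objective. A Month 0 to 14 count merges it with the vaccination-phase events already reported in the final analysis.

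For the coprimary endpoint, the question is whether more children on RTS,S/AS01E than on RTS,S/AS02D have an SAE. The plan replaces that with a series of tests on individual terms, each with few events. An excess that shows as a mixture of diagnoses is what such tests detect least well. Section 1.6 presents this trial as the safety step before studies in younger children and infants, so the coprimary safety endpoint should have a comparison of its own.

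**Working it through.** **1. Tertiary window (no assumptions needed).**

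| Source | Period |
|---|---|
| Objective 2.3, endpoint 10.3.2 | Month 3 to Month 14 |
| Analysis 10.8.1.1 | Study start to Month 3 |
| Analysis 10.9.1 | Study start to Month 14 |

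Let A be the children with an SAE up to Month 3 and B those with an SAE in Months 3 to 14. The cumulative analysis gives |A or B| = |A| + |B| − |A and B|. Subtracting the Month 3 result leaves |B| − |A and B|, the children whose only SAEs were late. This falls short of |B| by every child with SAEs in both periods, and the planned tables do not show that overlap.

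**2. Start of the coprimary window.** The endpoint starts at first vaccination, but the analysis starts at study start. Section 8.4 collects SAEs related to study participation from consent, so the two starting points can differ.

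**3. Power of the coprimary comparison.**

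The protocol's own safety power figures are in Table 11: 90% in each row with 75 per group. Exact enumeration of the two-sided Fisher test at 0.05 gives 79.9%, 83.6%, 80.6% and 80.0% at 75 per group, and 89.2%, 91.2%, 88.4% and 87.8% at 90. That discrepancy is a separate matter. Nothing below uses the 90%; two rows of the table are used only as example rates.

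Inputs:
- 90 per group (section 4.5), if all enrolled children are vaccinated.
- Two-sided Fisher test at 0.05 (section 10.5.1).
- SAE rates: the protocol gives none, so these are assumed.

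Method: power is the sum, over all pairs (i, j) with Fisher p ≤ 0.05, of Bin(i; 90, p1) × Bin(j; 90, p2). For m terms the total rate is divided evenly, with one term per child. The chance that at least one is significant is approximated as 1 − (1 − power per term)^m, treating the tests as independent.

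Smallest significant split with no cases in one group: 5 v 0 gives p = 0.059 and 6 v 0 gives p = 0.029. A term needs at least six affected children in the other group.

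Any SAE 5% v 20%:
- One any-SAE test: 84.7%.
- Five equal terms, 1% v 4% each: 7.2% per term; 1 − (1 − 0.072)^5 = 0.31.
- Ten equal terms, 0.5% v 2% each: 0.6% per term; 1 − (1 − 0.0062)^10 = 0.06.
- One term holding 60% of events (0.6 × 5% v 0.6 × 20% = 3% v 12%): 55% for that term.
- One term holding 80% of events (4% v 16%): 73% for that term.

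Two Table 11 rows used as any-SAE rates, split evenly:

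| Any-SAE rates | One test | At least one of 2 terms | of 4 | of 8 |
|---|---|---|---|---|
| 5% v 21% | 88.4% | 74% | 48% | 14% |
| 10% v 29% | 87.8% | 76% | 57% | 29% |

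**4. False positives.** At 90 per group, the exact type I error per term is 0.02% if the true rate is 1% in both groups, and 0.34% if it is 2%. Over 20 independent terms this is about 0.5% and 6.6%. It reaches about 31% only if all 20 terms have a 5% rate.

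**The case against.** The strongest reply is that no SAE hypothesis is being tested. The coprimary safety objective is only to assess safety, while the anti-CS objective is to demonstrate non-inferiority. Section 10.5.1 already concedes that only large differences can be detected, and no decision rule depends on an SAE p-value. The wording of 10.8.1.1 does not exclude an overall row, and section 6.5 promises a reporting and analysis plan that could add one. This lowers the weight of the coprimary half. It does not remove it, because the protocol does specify a between-group comparison and specifies it at a level other than that of the endpoint.

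The power loss also depends on an assumed even split. Section 4.3 describes intense malaria transmission, and malaria meeting the SAE criteria is reported as an SAE, so clustering in a few terms is plausible and the loss would then be smaller. This stands, and is why a range is given.

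A reader might infer that a real excess would probably be missed. The documents do not support that. The DSMB is notified of all SAEs within 24 hours (5.1.3), receives unblinded reports after Doses 1 and 2 (5.1.3.3), and can recommend suspension for a single SAE or a pattern (5.1.3.4). SAEs are also described in detail at study end.

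A reader might also infer that the many unadjusted tests make a chance finding likely. For rare terms they do not: the discreteness that costs power also holds the error down, as step 4 shows.

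On the tertiary half, the reply is that the endpoint is low in the hierarchy and descriptive. That makes the mismatch minor, but it remains a mismatch.

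**Conclusion.** Both mismatches stand on the text. The tertiary one needs no assumption: the Month 3 to 14 period named in the objective and endpoint has no estimate, and the planned tables cannot supply one.

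The coprimary one is that an any-SAE endpoint is compared only term by term. Its size rests on assumed rates and on how events spread. At 5% v 20%, about 85% power for one test compares with about 31% over five equal terms and 6% over ten; a single term holding 60% to 80% of events has 55% to 73%. These figures assume 90 vaccinated children per group, one term per child and approximate independence between terms.

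The point is about matching analysis to endpoint. It does not show that the trial would overlook a safety problem or report a spurious one. The changes should be made, but they are modest.

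**What to change.** - **Section 10.9.1:** add the proportion of children with at least one SAE with onset from Month 3 to Month 14, by group with exact 95% CI. Keep the cumulative table.
- **Section 10.8.1.1:** add the proportion of children with at least one SAE from Dose 1 (not study start) to Month 3, by group with exact 95% CI and one between-group comparison, for which the Fisher test already named will serve. Present the preferred-term tables as descriptive, and align the SAE comparison in 10.5.1.

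The cost is some wording and a few extra table rows. No additional children, visits or data are needed.

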#### **10.8.1.2. Secondary safety endpoints**

Safety will be analyzed on the Total Cohort.

The percentage of subjects with at least one local adverse event (solicited and unsolicited), with at least one general adverse event (solicited and unsolicited) and with any adverse event during the solicited follow-up period will be tabulated with exact 95% CI after each vaccine dose and overall. The percentage of doses followed by at least one local adverse event (solicited and unsolicited), by at least one general adverse event (solicited and unsolicited) and by any adverse event will be tabulated, overall vaccination course, with exact 95% CI. Similar tables will be generated for Grade 3 events, the relationship of the event to vaccination.

The percentage of subjects reporting each individual solicited local and general adverse event during the solicited follow-up period will be tabulated with exact 95% CI. The percentage of doses followed by each individual solicited local and general adverse event will be tabulated, overall vaccination course, with exact 95% CI. Similar tables will be generated for Grade 3 events, the relationship of the event to vaccination and for fever, temperature (in 0.5°C increments).

The proportion of subjects reporting an AE (unsolicited) 30 days post each vaccination, classified by the MedDRA preferred term level, reported from study start until the end of the double-blind phase (visit 6) will be tabulated with exact 95% CI.

Biochemistry (ALT, bilirubin, creatinine) and hematology (hemoglobin, WBC, platelets) values that are outside of the reference ranges will be described for Clinic Visit 6 (end of double-blind phase). Frequency distribution of results by toxicity grades will be tabulated by group.

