## **2. OBJECTIVES**

### **2.1. Coprimary objectives**

- For RTS,S/AS01E when administered as 3 doses intramuscularly on a 0, 1, 2-month schedule to children aged 18 months to 4 years living in a malaria-endemic area:
  - to assess safety until one month post Dose 3
  - to demonstrate non-inferiority to RTS,S/AS02D in terms of anti-CS antibody response one month post Dose 3.

Refer to Section 10.1 for definition of the coprimary endpoints.

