#### **4.5. Number of subjects**

Children will be recruited by non-coercive methods according to existing policies of the study site (see Appendix C).

The necessary number of children will be screened in order to enroll approximately 180 eligible subjects, 90 to each group. See Section 10.5 for a detailed description of the criteria used in the estimation of sample size.

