#### **5.4. Vaccination process**

The vaccines RTS,S/AS02D and RTS,S/AS01E will be packaged in identical boxes and will be identified by a treatment number. The unique treatment number will identify all doses of these vaccines administered to each subject. After randomization the treatment number assigns the subject to one group or another in a blinded way. Each subject will retain the same treatment number for their subsequent vaccine doses. The treatment number will be recorded on the subject's Clinic Form after the vaccine has been administered; information from the Clinic Form is subsequently transferred to the Case Report Form. The Clinic Form and Case Report Form link the subject number and the treatment number.

All vaccines will be administered by the intramuscular route to the left deltoid. Subjects who receive their vaccination in the incorrect arm will continue to receive subsequent blinded vaccinations as normal. The fact that the vaccine was administered in the wrong arm will be documented.

Vaccinations will take place at the HAS MRU or the outpatient clinic of HAS. All vaccinations will be given by a qualified person; a nurse or a doctor. A staff member experienced in the resuscitation of children will be available at all vaccination sessions. Facilities and equipment will be available to give emergency treatment in the case of an anaphylactic reaction following administration of vaccines. All children will be observed for an hour after the administration of vaccine to evaluate and treat any acute adverse events.

The process for each vaccination is as follows. The identity of the child will be confirmed using the study identification card. The subject number on this card will be cross-checked with that on the subject's clinic form, ensuring that the subject number on the clinic form matches that of the study identification card. On the day of the first vaccination the contraindications to vaccination, inclusion/exclusion criteria and ICF will be checked prior to vaccination. On the days of the subsequent vaccinations, elimination criteria and

contraindications to vaccination will be checked prior to vaccination. A vaccine clinic form will be initiated, which will give the child's identifiers, subject number and treatment number assigned after the administration of the vaccine.

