**10.5. Estimated sample size**

A sample size of 75 evaluable subjects per group will have 90% power to demonstrate non-inferiority of RTS,S/AS02D versus RTS,S/AS01E in terms of anti-CS immune response (upper limit of 95% CI of the GMC ratio RTS,S/AS02D versus RTS,S/AS01E below 3.0) assuming a log Standard Deviation of 0.9 in both groups, alpha=0.025 (Pass 2000). It will be considered that non-inferiority is reached when the upper limit of the 95% CI of the anti-CS GMC ratio of RTS,S/AS02D to RTS,S/AS01E is below 3.0.

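### The exact 95% CIs on percentages of doses ignore that each child contributes up to three doses, so they are too narrow if reactions within a child are positively correlated

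*Protocol*

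**What the plan says.** Protocol Section 10.8.1.2 (Secondary safety endpoints) sets two kinds of table, and the difference between them decides this point.

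- **Per subject.** For individual solicited events: "The percentage of subjects reporting each individual solicited local and general adverse event during the solicited follow-up period will be tabulated with exact 95% CI". Also planned, again with exact intervals, is the percentage of subjects with any local, any general or any adverse event, after each dose and overall.
- **Per dose.** For the same individual events: "The percentage of doses followed by each individual solicited local and general adverse event will be tabulated, overall vaccination course, with exact 95% CI". A matching per-dose row with an exact interval is set for any local, any general and any adverse event. The section extends the tables to Grade 3 events, to related events and, for fever, to temperature bands.

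The analysis set is stated as: "Safety will be analyzed on the Total Cohort".

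Three other places fix the data structure. Section 2.1 has the vaccine "administered as 3 doses intramuscularly on a 0, 1, 2-month schedule". Section 5.4 says: "Each subject will retain the same treatment number for their subsequent vaccine doses". Section 4.5 plans screening "in order to enroll approximately 180 eligible subjects, 90 to each group". So one child supplies up to three doses of one vaccine to the pooled denominator. Nothing in the protocol adjusts for that.

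**The concern.** An exact interval for a percentage, in the ordinary (Clopper-Pearson) sense, treats the count of events as binomial, with every observation independent. Pooled doses do not meet that condition by design. The same child, with the same susceptibility and the same household reporting, receives the same vaccine at each dose, so a child who reacts once is plausibly more likely to react again. For fever, Section 4.3 notes that malaria attack rates differ widely between children, and stable differences of that kind also correlate outcomes within a child.

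With positive correlation, 270 doses carry less information than 270 independent observations, and the stated 95% coverage is not delivered. Reactogenicity is a secondary objective (Section 2.2), and the Synopsis describes this as the first study to give RTS,S/AS01E to children, so readers will look at how precisely the reaction rates are known. The interval method is written into the protocol, so it is not a detail left open for the analysis plan.

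**Working it through.** The protocol states no per-dose interval, event rate or within-child correlation, so there is no figure of its own to reproduce.

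**Inputs from the protocol**
- Doses per child: 3 (Section 2.1).
- Children per group: 90 enrolled (Section 4.5), up to 90 × 3 = 270 doses. This is the relevant case, because safety uses the Total Cohort.
- Lower case: 75 evaluable per group (Section 10.5), up to 225 doses.

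**Assumptions, not in the protocol**
- Within-child correlation ρ from 0 to 0.5.
- True per-dose event rate from 5% to 50%.
- Every child receives all three doses.
- Exact means Clopper-Pearson.

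**Step 1: design effect.** With m = 3 doses per child, DE = 1 + (m − 1)ρ = 1 + 2ρ. The effective number of doses is 270/DE. The true standard error is √DE times the binomial one. Equivalently, the binomial one is too small by 1 − 1/√DE.

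**Step 2: coverage.** Beta-binomial simulation, 20,000 runs per setting, with the Clopper-Pearson interval computed on all doses. The ranges cover 75 and 90 children and rates of 5% to 50%.

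| ρ (assumed) | DE | Effective doses of 270 | True SE larger by | Binomial SE too small by | Coverage of nominal 95% CI |
|---|---|---|---|---|---|
| 0 | 1.0 | 270 | 0% | 0% | 95.5-97.2% |
| 0.1 | 1.2 | 225 | 10% | 9% | 93.3-95.3% |
| 0.2 | 1.4 | 193 | 18% | 15% | 91.1-93.4% |
| 0.3 | 1.6 | 169 | 26% | 21% | 88.8-91.3% |
| 0.5 | 2.0 | 135 | 41% | 29% | 84.2-87.7% |

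The Clopper-Pearson interval is conservative, which is why coverage starts above 95% at ρ = 0 and stays near 95% at ρ = 0.1 for low rates. From ρ = 0.2 upward it was below 95% at every rate tried.

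**Step 3: what a reader would see.** Take 81 of 270 doses (30%) followed by an event and recompute the exact interval on the effective number of doses.

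- As planned: 24.6% to 35.8%.
- ρ = 0.1: 24.1% to 36.4%.
- ρ = 0.2: 23.6% to 37.0%.
- ρ = 0.3: 23.2% to 37.5%.
- ρ = 0.5: 22.4% to 38.5%.

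For a rarer event, 14 of 270 doses (about 5%), the planned interval is 2.9% to 8.5%. At ρ = 0.3 it becomes 2.4% to 9.7%.

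**Step 4: comparison of the two groups by eye.** With equal groups and no true difference, two unadjusted 95% intervals fail to overlap when the absolute difference exceeds 2 × 1.96 binomial SEs. The true SD of the difference is √2 × √DE binomial SEs, so the cut-off in standard units is 1.96 × √2/√DE. This gives 2.77, 2.34, 2.19 and 1.96 at ρ = 0, 0.2, 0.3 and 0.5, or chance non-overlap of about 0.6%, 1.9%, 2.8% and 5%. Simulation with the actual exact intervals on 90 children per group gives lower values: 1.2-1.5%, 1.9-2.5% and 3.8-4.3% at ρ = 0.2, 0.3 and 0.5.

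**The case against.** The strongest reply is that little depends on these intervals, and most of it stands.

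- **Valid intervals sit beside them.** The per-subject tables cover the same events with one observation per child, and their exact intervals are correct. The per-dose rows are companions to them.
- **No decision uses them.** Section 10.8.1.2 attaches no test or margin. The primary safety analysis compares subjects with SAEs, and the coprimary non-inferiority test is on anti-CS titers (both Section 10.8.1.1). The fever criterion in Section 5.1.3.4 does count doses, but as a raw percentage without an interval.
- **The size is assumed.** The protocol gives no within-child correlation. At 0.1 or below, coverage stays at roughly 93% or above. With zero or negative correlation the intervals would not be too narrow at all.

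A reader might also infer that the two vaccines could often look different by chance, because their per-dose intervals fail to overlap. The calculation does not support that. Unadjusted intervals do raise the chance of false separation, but non-overlap of two 95% intervals is a strict criterion, and it stays at or below about 5% per comparison even at a correlation of 0.5.

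The reply does not remove the defect. The protocol names a method whose independence assumption the design does not meet, and positive correlation is the plausible case when one child receives one vaccine three times. Being descriptive limits the consequence, but an interval printed as 95% should still be close to 95%.

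**Conclusion.** The point holds, with limited consequence. The exact intervals on percentages of doses treat up to 270 doses from about 90 children per group as independent, and they are too narrow for any material positive within-child correlation. At assumed correlations of 0.2 to 0.5 the nominal 95% interval covers about 93% down to 84% of the time. At 0.1 the loss is slight.

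The direction rests on positive correlation, which is plausible but not documented. The size rests wholly on the assumed range. It would be wrong to read this as undermining the reactogenicity analysis as a whole, the safety conclusions or the suspension criteria: the per-subject and single-dose intervals are sound, and nothing inferential uses the pooled per-dose ones.

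**What to change.** In Section 10.8.1.2, for every percentage-of-doses row (any local, any general, any event, each solicited event, and the Grade 3, related and fever versions), replace the exact binomial interval with one that takes the child as the cluster. Suitable choices are:

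- GEE with robust variance, for events that are not sparse.
- A bootstrap that resamples children.
- An exact or Wilson interval on the design-effect-adjusted number of doses, for sparse events. Where too few events occur to estimate a correlation, using the number of children as the effective denominator (ρ = 1) is a conservative fallback.

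The method should be named in advance. The simpler alternative is to print the per-dose percentages without intervals and leave precision to the per-subject tables. Exact intervals should stay for the per-subject and single-dose tables.

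The cost is a change of wording, a little more programming and somewhat wider intervals: about 10% wider at a correlation of 0.1 and 42-46% wider at 0.5. Design, sample size and data collection do not change.
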